#### 2.4.1. Processing of Passive Behavioural Data from Sensors

Using validated algorithms, metrics will be extracted from the data of three sensors in both members of the dyad (for the daily and monthly scales): (1) metrics from the acceleration signal; (2) metrics from the skin conductance signal, and, (3) metrics from the Blood Volume Pulse (BVP) signal.

*Acceleration signal*: We will use a validated signal processing algorithm based on aggregation methods to extract «activity counts» from the raw data of acceleration. Using the validated Cole-Kripke algorithm (an automatic scoring method to distinguish sleep from wakefulness based on wrist actigraphy), we can also detect falling asleep and waking times from the acceleration signal.*Skin conductance signal*: Skin conductance data are traditionally interpreted using validated algorithms that extract two metrics: phasic skin conductance and tonic skin conductance. Phasic changes usually appear as abrupt increases (“peaks”) in the skin conductance. These are generally referred to as Galvanic Skin Responses (GSRs). Tonic skin conductance corresponds to the raw level of conductance of the skin and is usually referred to as Galvanic Skin Level (GSL). Further metrics such as storms (minimum of 5 GSRs/min for at least 10 consecutive minutes) can subsequently be derived from skin conductance data.*BVP signal*: The heart rate is computed by detecting peaks (beats) from the BVP data and computing the lengths of the intervals between adjacent beats. The inter-beat-interval (IBI) timing is used to estimate the instantaneous heart rate (HR), the average HR over multiple beats, and the heart rate variability (HRV) spectrum.

Aside from validated algorithms, we will also use functional principal component analysis (fPCA) to extract metrics from raw sensor data: strings of raw data for a given period can be fit with Fourier-based functions and the equations describing these fits are subjected to fPCA, which allows to reduce the complexity of the data sets through the extraction of only several components (see for instance Zeitzer et al. [29] using acceleration signals).

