### 2.8. Statistical Analyses

#### 2.8.1. Sample Size

The required sample size is estimated according to our primary objective of validation of a measurement model for the three assumed behavioural markers of apathy. We will use a Confirmatory Factor Analysis (CFA) based on Structural Equation Modelling and according to Westland [49]. For this kind of models, the required sample size depends on the ratio r = p/k where p is the number of observed indicator variables (i.e., the total number of metrics) and k is the number of unobserved latent variables in the model (i.e., the number of behavioural markers of apathy we want to measure through these metrics). Assuming that we can find 36 metrics for the measure of the three behavioural markers of apathy for one dyad, a ratio r = p/k = 36/3 = 12 would require a sample size of at least 50. We thus decided to recruit a total of 60 dyads, which is 20% more than this minimum sample size, to compensate for potential dropout of some dyads during follow-up. Besides, a total of 60 dyads seems to be a suitable sample size in terms of feasibility (given that we plan to complete the inclusions within a maximum of 24 months by recruiting 2 or 3 dyads per month). With this sample size (N = 60) for a model with p = 36 and k = 3 (591 degrees of freedom), the statistical power (i.e., the probability of rejecting the null hypothesis of a model with close fit when true model fit is mediocre) is quite satisfactory (π = 94.2%).

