#### 2.8.2. Analysis Plan for Primary Objective

First, we will extract the metrics from both passive and active behavioural data on a monthly and a daily basis for all dyads. Using these metrics, we will explore a measurement model for the three assumed behavioural markers of apathy on the two time-scales (with monthly scale metrics for the monthly scale model and daily scale metrics for the daily scale model).

We will use Exploratory Factor Analysis (EFA) and Confirmatory Factor Analysis (CFA) in order to identify the system of metrics organised between the three markers, which is the most adapted to measure them. Statistical criteria for the validation of the measurement model tested in CFA (i.e., Root Mean Square Error of Approximation < 0.08, Standardized Root Mean Square Residual < 0.08, Comparative Fit Index > 0.9, Tucker-Lewis Index > 0.9) will guarantee its good adjustment to the data. The internal consistency of the measures of the three behavioural markers will be assessed using Cronbach’s alpha (>0.70). The reliability of the measures (on a daily scale) will also be evaluated through the correlations between the behavioural marker scores obtained on four time-steps (once a week) during the 28-day follow-up (high correlation indicating high reliability).

We will compare the measurement models and mean scores on the three behavioural markers of apathy between groups of patient-caregiver dyads and control dyads (on two time-scales). We will demonstrate that the patient-caregiver dyad’s scores on the three assumed markers of apathy can predict the dyad’s psychological state (as perceived by the spouse caregiver) using linear regression models on the monthly and daily scales. In a perspective of precision medicine, we will also investigate the disentangling of different profiles of apathy, using clustering analyses from the calculated behavioural markers of apathy.

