Another potential measurement bias can be underlined in the assessment of behavioural markers of apathy through metrics from passive data of both individuals with dementia and their caregiver. Residual errors of prediction for the passive behavioural metrics aimed at measuring one behavioural marker will not be independent from each other and identically distributed: in particular, the residual errors relative to the caregivers’ metrics are likely to be covariates and so are the residual errors relative to the patients’ metrics. These covariances will have to be taken into account in the statistical modelling. It is also possible that the metrics extracted for both partners of one dyad are not sufficiently correlated to correspond to the measure of the same latent behavioural marker (especially for patient-caregiver dyads). If so, behavioural markers of apathy will need to be assessed using only the patient’s passive behavioural data instead of both the patient’s and caregiver’s passive behavioural data.

Finally, it seems difficult to estimate the extent of the measurement bias that might be introduced by the support provided to the caregiver through the study follow-up in an objective way. We could try to investigate a potential modification of signals from sensors worn by the caregiver between before and after a phone call with the investigator. However, we expect that this impact can be neglected (only two phone calls are scheduled with the investigator, and this is mostly for technical support).

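### The Cronbach's alpha > 0.70 criterion is inconsistent with the correlated residuals that the protocol predicts, and overstates reliability for the shared marker by an amount the protocol does not let us fix

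*Protocol article*

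**What the plan says.** Section 2.8.2 (Analysis Plan for Primary Objective) gives the coefficient and its threshold: "The internal consistency of the measures of the three behavioural markers will be assessed using Cronbach’s alpha (>0.70". For the daily scale only, it adds a second reliability check "through the correlations between the behavioural marker scores obtained on four time-steps", with no threshold.

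Section 3.2 (Potential Limitations of the Project) says of the residuals of passive metrics aimed at one marker that they "will not be independent from each other and identically distributed". It then specifies the pattern: "the residual errors relative to the caregivers’ metrics are likely to be covariates and so are the residual errors relative to the patients’ metrics". The consequence it draws is "These covariances will have to be taken into account in the statistical modelling". It does not mention alpha. It also provides a fallback: if the two partners' metrics correlate too weakly to reflect one marker, only the patient's passive data will be used. No numerical trigger is given.

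On the number of metrics, section 2.8.1 (Sample Size) says "Assuming that we can find 36 metrics for the measure of the three behavioural markers of apathy for one dyad". Section 2.4.1 says that passive metrics are extracted "in both members of the dyad (for the daily and monthly scales". Section 2.4 says that the monthly scale uses passive data only.

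**The concern.** Alpha equals the reliability of a sum score when metrics load equally on the factor and residuals are uncorrelated. Where residuals covary positively, alpha treats the covariance as marker signal. The CFA that section 3.2 calls for would treat the same covariance as error. The two parts of the plan therefore give different meanings to one quantity.

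The covariance follows from the design. Each marker combines metrics from two people, and several metrics are functions of one signal. Section 2.4.3, for example, takes mean activity counts, activity bouts and sedentary bouts all from the accelerometer.

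Reliability is one of the two psychometric properties named in the primary objective (section 2.1.1), and the marker scores feed the group comparisons, regressions and clustering. On the monthly scale there is one score per dyad, so alpha is the only reliability coefficient stated. An inflated value there could present a score as reliable for the dyad's marker when much of its variance is specific to one person or one sensor.

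**Working it through.** **The plan's own figures.** The protocol gives no figure for reliability under correlated residuals. Its model size can be reproduced: "With this sample size (N = 60) for a model with p = 36 and k = 3 (591 degrees of freedom". There are 36 × 37 / 2 = 666 moments. Taking off 36 loadings, 36 residual variances and 3 factor covariances (75 parameters) leaves 591. That model contains no residual covariances.

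**Inputs.**
- 36 metrics and 3 markers (section 2.8.1), so 36 / 3 = 12 per marker on average.
- Assumed: 6 metrics per partner, equal standardised loadings λ, and equal same-person residual correlation ρ. None of these is in the document, so a range is shown.

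**Formulas.** With K = 12 metrics, m = 6 per partner and residual covariance c = ρ(1 − λ²), the variance of the sum score is

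V = K + K(K − 1)λ² + 2m(m − 1)c = 12 + 132λ² + 60c.

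Alpha = (12/11)(1 − 12/V). Omega, the share of V due to the marker, = 144λ²/V.

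**Worked case.** For λ = 0.3 and ρ = 0.3, c = 0.3 × 0.91 = 0.273 and V = 12 + 11.88 + 16.38 = 40.26. Alpha = (12/11)(1 − 12/40.26) = 0.77. Omega = 12.96/40.26 = 0.32.

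**Range (alpha / omega).**

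| Loading λ | ρ = 0 | ρ = 0.2 | ρ = 0.3 | ρ = 0.4 |
|---|---|---|---|---|
| 0.3 | 0.54 / 0.54 | 0.71 / 0.37 | 0.77 / 0.32 | 0.80 / 0.28 |
| 0.4 | 0.70 / 0.70 | 0.79 / 0.53 | 0.82 / 0.48 | 0.85 / 0.43 |
| 0.5 | 0.80 / 0.80 | 0.85 / 0.67 | 0.87 / 0.62 | 0.88 / 0.57 |
| 0.6 | 0.87 / 0.87 | 0.90 / 0.77 | 0.91 / 0.73 | 0.92 / 0.69 |

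The coefficients agree when residuals are uncorrelated. As ρ rises, alpha goes up and omega goes down. At λ = 0.3, alpha fails without residual correlation and passes with it, although the marker contributes no more variance.

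**How low the bar is.** Solving 0.70 = 12r/(1 + 11r) gives r = 0.7/4.3 = 0.163. With 12 metrics, a mean inter-metric correlation of 0.163 is enough.

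**At the planned sample size.** Take a correlation of 0.10 between partners' metrics and 0.50 within a person (residual covariance 0.40). Then V = 12 + 13.2 + 24 = 49.2, alpha = 0.825 and omega = 14.4/49.2 = 0.293. In 4,000 simulated samples of 60 dyads, sample alpha exceeded 0.70 in 99%. With both correlations at 0.10 (alpha = omega = 0.571) it did so in 2.5%.

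**Do the fit indices catch it?** A one-factor model without residual covariances, fitted to four such structures, gave RMSEA of 0.10 to 0.20, so it fails the 0.08 limit. Once the covariances are modelled, as section 3.2 requires, the model fits. Alpha does not change, because it is computed from the metrics and not from the model.

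**Under the patient-only fallback.** Assume 12 patient metrics in 3 sensor clusters of 4, with correlation 0.10 between clusters and 0.70 within. V = 12 + 13.2 + 36 × 0.60 = 46.8, alpha = 0.81 and omega = 14.4/46.8 = 0.31. With only 6 metrics in 3 clusters of 2, V = 6 + 3 + 3.6 = 12.6 and alpha = 1.2(1 − 6/12.6) = 0.63, which fails. With 0.20 between clusters instead, V = 6 + 6 + 3 = 15, alpha = 0.72 and omega = 7.2/15 = 0.48.

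**The case against.** **The size rests on chosen inputs.** This stands. Loadings, residual correlations and the 6 + 6 split are all assumed. With strong loadings the two coefficients give nearly the same answer. The equal split also suits the daily scale less well, because questionnaire metrics are added there and in patient-caregiver dyads they describe the patient only.

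**The worst case is one the protocol foresees.** Loadings of 0.3 imply a correlation of 0.09 between partners' metrics, which is when section 3.2 would switch to patient-only data. Covariance within the patient is then largely the marker itself, and the person-level inflation shrinks. This stands in part. The switch has no cut-off, and same-sensor covariance remains.

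**Alpha is one criterion among several.** This also stands. A reader might infer that passing alpha certifies a marker. The protocol does not say so: four fit thresholds, group comparison and prediction of caregiver ratings sit beside alpha, and weak loadings would be visible in the CFA output. But none of these is a reliability coefficient on the monthly scale.

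**Some same-person covariance may be true marker variance.** Fair; what counts as error is a modelling choice. Section 3.2, however, already calls it residual error, and alpha should follow the same definition.

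**The weekly correlations.** A reader might infer that these are inflated too, by pooling patients and controls. The protocol does not say whether they are pooled or taken by group, and it gives no figures from which to size such an effect. That point is not made here.

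**Conclusion.** The inconsistency is real. Section 2.8.2 applies a coefficient that is a reliability only without correlated residuals, while section 3.2 predicts such residuals and requires them in the model. If they are positive, alpha overstates reliability for the shared marker.

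Under the stated assumptions (12 metrics, 6 per partner, residual correlation 0.2 to 0.4), alpha clears 0.70 throughout. Omega is 0.37 to 0.28 at loadings of 0.3, 0.53 to 0.43 at 0.4, 0.67 to 0.57 at 0.5 and 0.77 to 0.69 at 0.6. The pass is misleading at loadings up to about 0.5 and mostly harmless at 0.6.

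A reader might go further and infer that markers with reliability near 0.3 will pass. The document does not support that as a prediction. It is the low end of an assumed range, and it falls where the patient-only fallback might apply. The monthly scale is the clearest case, because it uses passive data only and has no other reliability coefficient.

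**What to change.** Apply the 0.70 criterion to McDonald's omega for each marker, computed from the fitted CFA on standardised metrics with residual covariances kept in the denominator, and report a confidence interval. Alpha may be shown beside it.

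State the residual structure in advance and constrain it. Free same-person covariances within each marker would add 15 per partner, so 15 × 2 × 3 = 90 parameters to the existing 75, with 60 dyads. That is not feasible. One method factor per partner or per sensor, or equal residual covariances, would keep the model estimable. If only patient data are used, the structure should be by sensor, since a patient factor cannot then be told apart from the marker. A numerical trigger for the patient-only fallback should be stated too.

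No new data are needed. The costs are a reliability figure that may be lower and less precise than alpha, and a choice of residual structure that has to be justified before the data are seen.

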## 2. Materials and Methods

### 2.1. Objectives and Hypotheses of the Study

#### 2.1.1. Primary Objectives and Hypotheses

The main objective of ECOCAPTURE@HOME is to validate a measurement method to assess assumed behavioural markers of apathy in everyday-life conditions from data collected in patient-caregiver couples. We will attempt to identify the most fitted measurement model that ensures good psychometric properties (reliability and validity) for the measure of assumed behavioural markers of apathy. More precisely, we will validate two measurement models corresponding to two time-scales: across one month (28 days) and across one day. This will allow us to adjust according to the specific needs of clinicians regarding apathy telemonitoring: either short-term follow-up with daily measures or long-term follow-up with monthly measures.

Regarding this first central objective, we suggest three main hypotheses: the first one regarding the nature of assumed behavioural markers of apathy, the second one relative to the nature of the data required to assess these markers and the third one concerning the criteria used to guarantee their validity.

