#### 2.8.3. Analysis Plan for Secondary Objectives

A.We will investigate the links between the extracted behavioural markers of apathy in real-life conditions and the self-reported measures of apathy using a linear regression. We may also compare the clusters of individuals with dementia identified based on the behavioural markers with those based on the self-reported measures of apathy (DAS subscales in particular).B.We will analyse the impact of caregiver’s perception of the dyad’s psychological status on the subsequent behavioural markers of apathy using a linear regression to show that the caregiver’s perception at day N predicts the three behavioural markers of apathy at day N + 1 (i.e., one week later) above and beyond the markers of apathy at day N.C.We also will study the relationships between the patient’s and his/her caregiver’s passive behavioural data using Granger causality test (to investigate causality between two variables in a time series) applied to the different sensor signals collected for 28 days in patient-caregiver dyads.D.We will attempt to show that passive behavioural data can predict active behavioural data collected on a daily scale. For this purpose, we will create categories derived from the active behavioural data (for instance, good–medium–bad day from the caregiver’s point of view) and use different supervised clustering methods (Linear Discriminant Analysis, Random Forest, Support Vector Machine, Artificial Neural Networks, K-Nearest Neighbours) to investigate their capacity to predict the correct category from the set of passive behavioural data.

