## 3. Expected Results and Discussion

### 3.1. Expected Results

We expect to identify a fitted measurement model for daytime activity, quality of sleep and emotional arousal from the collected passive and active data in all dyads. This will be the starting point to obtain scores for these three behavioural markers of apathy in each dyad (four scores on a daily scale and one score on a monthly scale). Scores of daytime activity, quality of sleep and emotional arousal are expected to be highly correlated and to distinguish patient-caregiver couples from healthy control couples. Besides, these scores should all contribute to predict the caregiver’s perception regarding the patient’s apathy and regarding his/her own burden and quality of life. Finally, we expect to identify different apathy profiles based on the extracted scores of daytime activity, quality of sleep, and emotional arousal. In particular, as emotional apathy has been shown to be greater in bvFTD than in AD [17,18], we should observe a profile characterized by very low emotional arousal in bvFTD.

Regarding the secondary objectives, we expect to be able to identify which behavioural marker (daytime activity, quality of sleep, or emotional arousal) best predicts the different self-reported measures of apathy. In particular, we can expect the initiation (or auto-activation) component of apathy (DAS-Initiation) to be specifically related to daytime activity whereas the emotional apathy subtype (DAS-Emotional) should be more linked with emotional arousal. Moreover, we globally expect to provide evidence of a close and reciprocal relationship between the patient’s behaviour/status and caregiver’s behaviour/status (e.g., strong causal impact between patient’s and caregiver’s physiological status assessed by sensor data). The caregiver’s state should have an impact on the subsequent measure of daytime activity, quality of sleep, and emotional arousal and reciprocally.

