### 3.3. Potential Impacts of the Project

The aim of this protocol is to lay the foundations for a system capable of remotely monitoring the evolution of apathy in individuals with dementia and the associated impact on their caregiver. This system would provide a measure of behavioural markers of apathy that is completely independent of the patient’s self-report and thus not impacted by the patient’s subjective bias and anosognosia. Building on the knowledge acquired through this first ECOCAPTURE@HOME study, we expect that the following step of such a process will be to test a machine learning system which could, after a training period, automatically estimate the behavioural markers of apathy and the associated caregiver’s perception of the dyad’s status, using solely passive data from sensors. This system could present several interesting applications for clinicians and in particular neurologists. Firstly, this monitoring system could allow for the remote evaluation of the evolution of the patient-caregiver dyads’ psychological state, thus improving the potential for detection and prevention of dangerous situations such as caregiver burn out. Moreover, it could be used as a diagnostic tool providing information about a patient’s specific profile on the different behavioural markers of apathy and on how it is related with caregiver’s psychological status. This could prove useful for the implementation of new treatments adapted to a couple’s specific characteristics. In particular, by enabling the daily assessment of behavioural markers of apathy and associated dyad’s psychological health status, this system could be of great use to test and adapt therapeutic interventions accordingly in patients’ homes.

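### The four-week correlation of daily-scale scores measures stability of differences between dyads: it bounds reliability from below and cannot show whether change within a dyad is measured

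*Protocol article*

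**What the plan says.** All references are to the protocol article. Section 2.8.2 names two checks on the marker scores.

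- Internal consistency: "The internal consistency of the measures of the three behavioural markers will be assessed using Cronbach’s alpha (>0.70" is the stated mark.
- For the daily scale, in addition: "correlations between the behavioural marker scores obtained on four time-steps (once a week) during the 28-day follow-up (high correlation indicating high reliability". No cut-off and no decision rule is attached.

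Section 2.1.1 makes reliability and validity of two measurement models, monthly and daily, the primary objective. It explains the pair by clinical need: "either short-term follow-up with daily measures or long-term follow-up with monthly measures". Section 3.1 expects four daily-scale scores and one monthly score per dyad.

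Other sections expect the markers to move between weekly measurements. Analysis B in section 2.8.3 takes the caregiver's rating on one questionnaire day and tests whether it "predicts the three behavioural markers of apathy at day N + 1 (i.e., one week later) above and beyond the markers of apathy at day N". Section 3.1 adds: "The caregiver’s state should have an impact on the subsequent measure of daytime activity, quality of sleep, and emotional arousal and reciprocally". Section 3.3 looks ahead to "enabling the daily assessment of behavioural markers of apathy" and says that "this system could be of great use to test and adapt therapeutic interventions accordingly in patients’ homes".

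**The concern.** A test-retest correlation estimates reliability only if the true score stays put between occasions. Here the occasions are a week apart, and the plan itself expects the true score to move over that interval. Real change in a dyad's state then lowers the correlation just as measurement error does, while a score carrying nothing but a fixed dyad level does well.

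Two readings of the result are at stake. A low correlation may be taken as poor measurement when it reflects true change. A high one may be taken as support for using the daily score to follow a dyad over time, which it cannot give. The text fixes the interpretation as well as the statistic, so this is not a detail left to a fuller analysis plan.

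**Working it through.** **Plan's own figure.** None is given for this correlation. The article's only power figure (94.2%, N = 60, 591 degrees of freedom) concerns model fit and does not enter here.

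**Model.** Write a daily-scale score as T + S + E: stable dyad level, true state on that day, error. S and E are taken as independent across weeks. The documents give no variance shares, so all shares below are assumed and total 1.

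- Week-to-week correlation: r = T/(T+S+E)
- Reliability of the day's score: (T+S)/(T+S+E)
- Reliability of within-dyad change: S/(S+E)

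S sits in the denominator of r but not in its numerator, so r cannot exceed the day-score reliability. The two are equal when S = 0.

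| T / S / E | r | Day-score reliability | Within-dyad reliability |
|---|---|---|---|
| 0.90 / 0 / 0.10 | 0.90 | 0.90 | 0 |
| 0.80 / 0 / 0.20 | 0.80 | 0.80 | 0 |
| 0.45 / 0.45 / 0.10 | 0.45 | 0.90 | 0.45/0.55 = 0.82 |
| 0.30 / 0.60 / 0.10 | 0.30 | 0.90 | 0.60/0.70 = 0.86 |
| 0.70 / 0.20 / 0.10 | 0.70 | 0.90 | 0.20/0.30 = 0.67 |
| 0.80 / 0.15 / 0.05 | 0.80 | 0.95 | 0.15/0.20 = 0.75 |

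Rows 2 and 6 have the same r of 0.80; one marker carries no information on change and the other tracks it well. Rows 1 and 3 have the same day-score reliability, but r is twice as high in the one that is blind to change.

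**Sampling variation.** In 4,000 simulated studies of 60 dyads and four weeks, the mean of the six pairwise correlations had a 95% range of 0.72 to 0.86 for row 2, 0.71 to 0.86 for row 6, and 0.16 to 0.43 for row 4. Rows 2 and 6 cannot be told apart by r.

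**Cronbach's alpha.** If a marker's metrics are equivalent and their errors independent, alpha across dyads estimates (T+S)/(T+S+E). That is 0.90 for row 1 and 0.90 for row 3. Alpha above 0.70 is met in both, so alpha does not separate the two levels either.

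**Analysis B.** The share of marker variance not explained by the previous week's marker is 1 − r²: 1 − 0.49 = 51% at r = 0.70, 1 − 0.64 = 36% at r = 0.80, and 1 − 0.81 = 19% at r = 0.90.

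**The case against.** The strongest reply is that the correlation is not the only check. Alpha is a same-day coefficient and would credit an accurate day score whose r is low. The daily regression on the caregiver's visual analogue ratings is a further test. This stands: a good daily measure would not be condemned by r alone. But alpha mixes the two levels, and the regression addresses validity. Under the model, only the gap between the two coefficients carries the within-dyad information: (alpha − r)/(1 − r) is (0.90 − 0.45)/0.55 = 0.82 in row 3 and (0.90 − 0.90)/0.10 = 0 in row 1. The plan does not compare them; it reads each as better when higher.

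Four stronger readings are tempting, and the documents do not support them.

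- *A change-blind marker passes and an accurate one fails.* No cut-off is stated, so nothing passes or fails. With shares 60/30/10, an assumed mark of 0.70 is met in 3% of simulated studies and a mark of 0.50 in 94%. Row 6 shows an accurate, change-tracking marker with a high r. Pooling patient and control dyads also raises r: an assumed 1-SD group difference (40 against 20 dyads) adds variance of (2/3)(1/3) = 0.22, and row 3 becomes (0.45 + 0.22)/1.22 = 0.55.
- *A high r is misleading about the day's score.* It is not. High r is valid evidence that the day's score is reliable; in row 1 both are 0.90. It is silent only about within-dyad change.
- *The correlation measures how little scores change.* It measures stability of relative standing. A common shift of 1 SD per week left r at 0.80 in simulation.
- *Analysis B has nothing left to predict.* At r = 0.70, 51% of the variance remains. The two analyses pull against each other but do not exclude each other.

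It is also fair that adapting interventions is a future application, not a claim of this observational study. Short-term follow-up, however, is the stated reason for the daily model.

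**Conclusion.** The concern holds in a limited form. The four-week correlation is a stability coefficient: a lower bound on day-score reliability and uninformative about within-dyad change. Reading high as reliable is defensible for the day's score. Treating low as unreliable is not, and neither this correlation nor across-dyad alpha shows that the daily score can follow a dyad over time.

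The size depends on variance shares that the documents do not give. Over the assumed range with error fixed at 10%, day-score reliability stays at 0.90 while r runs from 0.30 to 0.90. A change-tracking marker is rated low only where within-dyad variance is large relative to between-dyad variance.

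The result assumes day states and errors independent across weeks. Positive persistence of the day state would raise r. Error that persists across weeks, such as a constant rater bias, would be counted as T, and r would then no longer be a safe lower bound.

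**What to change.** In section 2.8.2:

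1. Report the four-week correlation, or an ICC, as stability of between-dyad differences. State that a low value is not by itself evidence of unreliability.
2. Add a two-level (dyad, day) reliability of each marker score from the same-day metrics, such as multilevel omega or alpha, with separate between-dyad and within-dyad figures. Working across metrics is preferable to splitting the day by hours, which does not suit sleep and mealtime metrics.
3. Use the four questionnaire days for the full daily score, since it needs active data. As a supplement, use all 28 days for the passive-only part.
4. Base any statement that the daily score can follow change on the within-dyad figure.

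No new data are needed; the cost is wording and moderate programming. The within-dyad estimate from four days will be imprecise: 60 dyads give 60 × 3 = 180 within-dyad degrees of freedom, and 50 give 150. Errors shared by all metrics on a day, such as bracelet placement, can inflate it. The figure may also be less favourable than the weekly correlation.
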